## Abstract

**Introduction:**

Childhood stressors and adverse experiences can increase the likelihood of children developing mental disorders. The development of mindfulness-based cognitive therapy for children (MBCT-C) offers opportunities to improve emotional resiliency and reduce these children's vulnerabilities. The current study introduces the framework of a future clinical trial that seeks to examine the level of satisfaction and the efficacy of MBCT-C on anxiety, attentional control, and emotional regulation in children.

**Method:**

This research protocol outlines a quasi-experimental design that compares MBCT-C with an active control group. The intervention group will participate in a 12-session MBCT-C program, while the active control group will receive a 12-session program of life skills training (LST). Eighty children aged between 8 and 12 years will be randomly assigned to the intervention or the control group. Data using the Mindful Attention Awareness Scale for Children (MAAS-C), the Emotion Regulation Checklist (ERC), the State-Trait Anxiety Inventory for Children (STAI-CH), and the Attentional Control Scale for Children (ACS-C) will be collected at three times: baseline, post-intervention, and six months following the intervention. The Mindfulness Program Satisfaction Questionnaire (MPSQ) will assess participant satisfaction with the program. The effectiveness of MBCT-C will be evaluated using a conditional mixed regression model in STATA-18.

**Discussion:**

Providing a research protocol to conduct a clinical trial on MBCT-C before the intervention phase provides a precise evaluation of the goals and hypotheses, study method, assessment tools, and treatment outcomes.

## Introduction

Children frequently experience emotional problems, such as anxiety disorders (e.g., generalized anxiety disorder, separation anxiety), depression, obsessive-compulsive disorder, and disruptive mood regulation disorder in middle and late childhood (1, 2). Approximately 11.63% of children and adolescents worldwide meet the established criteria for a mental disorder (3), although it is essential to note that the prevalence of subclinical problems, particularly anxiety, is considerably greater (4). Mental problems experienced during childhood are often persistent and frequently continue into adulthood (5). Hence, it is imperative to consider the implementation of psychological interventions that enhance childhood resiliency and reduce the risk of subsequent internalizing and externalizing disorders (6, 7). Along with the contributing role of anxiety, emotion regulation (1, 8, 9) and attentional control (10) have been proposed as underlying factors in the psychopathology of children's emotional problems.

Anxiety is a future-oriented response to perceived threatening situations that are often characterized by ambiguity and uncertainty. Anxiety is a common, sometimes uncomfortable emotional experience. Only when it becomes severe is it considered a manifestation of psychological problems (11, 12). Chronic, uncontrollable anxiety can result in clinical distress and impaired performance (13, 14). Children often experience anxiety due to a wide range of transient or long-term stressors, which can be exacerbated by a limited capacity to effectively cope with such challenges (15, 16). When anxiety becomes severe, it impairs daily functioning, including social and school achievements (14, 17). For example, some children experience separation anxiety when they begin attending school, as they are separated from their parents and enter an unfamiliar environment (18). Others may feel socially anxious, fearing observation and negative judgements from others in social settings, which can lead to avoidance of many situations that require interpersonal interactions (19). Specific phobias also lead to avoidance of the source of fear and inability to tolerate the associated anxiety (20). Along with math (21) and test anxieties (22), which result in low grades and academic failure in children, these are common anxieties impair children's development.

Emotion regulation (ER) is an adaptive manner of managing emotions and feelings (8). ER capacity affects the interpretation of experiences, emotional expression, and responses to the emotions of others (23). Maladaptive coping strategies can disrupt emotion processing and aggravate emotional disturbances (8, 24, 25). Inadequate ER has received increasing attention as an underlying factor in childhood and adolescent mental disorders (26). Children who develop adaptive emotion regulation skills are more likely to have a better quality of life and are at lower risk for mental disorders (27). Strengthening ER skills is considered a preventive approach and a treatment goal to address emotional problems in children (26, 28). In one study, an ER-focused preventive intervention resulted in significant increases in emotional awareness, reductions in negative emotions, and reductions in internalizing problems in preschool children at risk for psychological problems (29). A recent meta-analysis found that a variety of psychosocial interventions were moderately effective in improving ER in children, adolescents, and transition-age youth (30).

Information processing in the human cognitive system takes place through the mechanism of attention control (AC). AC mechanisms facilitate the ability to direct and shift attention between stimuli and situations (31), selectively focusing on task-relevant information while ignoring irrelevant information (32). Difficulties managing attention to emotional and non-emotional stimuli have been associated with anxiety disorders and depression (33).

Cognitive processing deficits, especially the inability to shift attention from distressing thoughts, contribute to the persistence and exacerbation of worry and rumination (34, 35). Evidence supports the correlation of anxiety and depression with lower AC in children (36). The role of AC deficits is apparent in attention deficit hyperactivity disorder (ADHD) and some developmental problems (e.g., autism spectrum disorder) (37). A systematic review has provided evidence suggesting that enhancing attention capabilities contributes to a decrease in anxiety and depression (38).

The development of effective psychotherapies aimed at addressing emotional problems in children has made significant progress (14, 16, 39). Mindfulness-based interventions, in particular, are of growing interest. Mindfulness is an approach to life experiences that emphasizes attention to the present moment and with an attitude of non-judgment (40). Mindfulness, cultivated through meditation, involves bringing awareness to one's thoughts, emotions, and bodily sensations without engaging reactively to them (41, 42). Mindfulness-based interventions, which have been influential in evolving the third wave of cognitive-behavioral therapies, were developed initially for adults, but have now been adapted for children (43).

Mindfulness-based cognitive therapy (MBCT) was developed for relapse prevention in adult patients with recurrent depressive episodes (44, 45), and was later adapted for other problems and populations (46). One of these adaptations, MBCT-C, employs the same methodology as the adult program and shares analogous goals and objectives; however, it has been specifically tailored for children, which includes modifications to the duration of the sessions and the incorporation of child-friendly language and content (47). MBCT-C may be an effective intervention in mitigating emotional difficulties among children and adolescents (48, 49). A study conducted to investigate the effectiveness of MBCT-C on children and adolescents suffering from anxiety disorders who were at risk of bipolar disorder revealed that MBCT-C is effective in reducing clinical symptoms. Additionally, improvements in mindfulness were associated with improvements in anxiety and emotion regulation (50). The effectiveness of MBCT-C has been repeated in other clinical samples, including children with math anxieties (51), cancer (39), and internalizing disorders (52). The results of a meta-analysis, which compiled results from 3,977 child and adolescent mindfulness-based interventions, showed that the effect size of these interventions is small to moderate, and that the effectiveness appears to vary based on two factors: the type of facilitator and the characteristics of the program (53). Therefore, mindfulness-based interventions for children and adolescents in both clinical and non-clinical populations need further evaluation.

Children's clinical intervention programs should not be limited to clinical populations; their prophylactic effectiveness should also be examined in non-clinical populations. These programs may have significant benefits in preventing childhood problems (54). The primary aim of the present study protocol is to outline the theoretical framework and methodology of a quasi-experimental study to investigate the effectiveness of MBCT-C in managing non-clinical anxiety, emotion regulation, and attentional control in children. Five hypotheses are proposed:

Primary hypothesis
1.Following a 12-session MBCT-C program, children in this group will report significantly increased mindfulness compared to children attending a 12-session Life Skills Training (LST) program, as measured by the Mindful Attention Awareness Scale for Children (MAAS-C).Secondary hypotheses
2.Following a 12-session MBCT-C program, children in this group will report the MBCT-C group will report significant decreases in state and trait anxiety as compared to children attending a 12-session LST program, as measured by the State-Trait Anxiety Inventory for Children (STAI-CH).3.Following a 12-session MBCT-C program, children in this group will report a significant increase in emotion regulation as compared to children attending a 12-session LST program, as measured by the Emotion Regulation Checklist (ERC).4.Following a 12-session MBCT-C program, participants in this cohort will report a significant increase in attentional control when compared to children participating in a 12-session LST program, as measured by the Attention Control Scale for Children (ACS-C).5.The MBCT-C program will be acceptable to children and their parents as measured by recruitment, attendance, drop-out rates, and the Mindfulness Program Satisfaction Questionnaire (MPSQ).

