## Method

### Study design

This is a quasi-experimental study that comparing an MBCT-C program to an active control groupthe. Demographic data will be collected at baseline. Assessment data will be collected at baseline (T1), post-intervention (T2), and 6-month follow-up (T3) (Figure 1). Participants will be randomly assigned to either MBCT-C or LST using a software-generated random sequence. A stratified block randomization method will ensure balanced distribution by gender and age. A comparison of attendance and drop-out rates between the MBCT-C and LST groups will be one marker of program acceptability. Participants' adherence to the intervention will be evaluated via session attendance, group activity participation, and homework assignment compliance. To reduce potential bias, assessors will be blind to group allocation.

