### Recruitment and randomization procedures

In this study, our sampling framework encompasses four schools (two female-only and two male-only institutions) randomly selected from diverse districts across Tehran to ensure appropriate population representation. The target population comprises all middle school students in Tehran who, according to Iran's educational system, attend gender-segregated schools.

The necessary research permits will be obtained from Tehran's Education Department through the university's Research Vice-Chancellor's office. Group intervention sessions will be conducted after regular school hours in the counseling rooms of the participating schools, providing a quiet and appropriate environment for group therapeutic activities. This approach facilitates student access to the program while avoiding interference with their academic schedules.

Furthermore, school counselors will explain the research and introduce interested parents and students to the research team. Should these recruitment techniques be insufficient to obtain the desired sample size within a reasonable time, we will extend recruitment to additional schools within the Tehran education district.

Potential participants who contact the research assessment team will undergo an in-person screening to determine their eligibility. Inclusion criteria include: (a) primary school students, (b) age between 8 and 12 years old, (c) living in Tehran, and (d) ability to speak Persian. Exclusion criteria comprise (a) reporting an acute physical illness, (c) receiving psychotropic medications, and (e) receiving concurrent psychotherapy. Children who meet the criteria for this study and agree to participate will be enrolled with the consent of a parent or caregiver. Once the desired sample size is enrolled, participants will be randomized to the MBCT-C or LST group using online random allocation software (https://miniwebtool.com/de/number-randomizer/). The allocation will be made in a 1:1 ratio, ensuring equal representation of participants in each group.

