### Procedure

Participants will be recruited from public elementary schools in Tehran. We will employ a staged recruitment approach, enrolling four cohorts of 20 children each (80 total). As each cohort of 20 children is recruited, they will be randomly assigned to either intervention or control groups (10 per group), and the 12-week programs will begin. While the first cohort undergoes treatment, recruitment for subsequent cohorts will continue.

Interested children will participate in a brief eligibility screening. Eligible students and their parents will receive comprehensive information about the study. Participation requires written informed consent from a parent or guardian and verbal assent from the child. Participants assigned to the intervention group will attend weekly 90-minute MBCT-C sessions for 12 weeks. The control group will participate in a 12-week LST program. Each program will be facilitated by separate instructors trained and invested in their respective models to prevent potential bias.

Protocol adherence will be monitored using the MBCT-C adherence scale and an equivalent measure for LST. A trained supervisor will review recorded sessions and provide feedback to facilitators to ensure standardized protocol implementation. Participants will complete the T2 assessment battery at the end of the intervention and the T3 follow-up assessment six months later. The Client Satisfaction Questionnaire (CSQ-8) will measure participant satisfaction with both programs.

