### Satisfaction and adherence measures

#### Mindfulness program satisfaction questionnaire (MPSQ)

MPSQ was developed by Semple (2016) using the items of the original version of the Client Satisfaction Questionnaire [CSQ (71)]. It includes 8 items rated on a 4-point Likert scale. Half of the items are scored directly (including 5, 4, 2, and 8), and the other half is scored in reverse (1, 3, 6, and 7). Scores range from 8 to 32, and higher scores indicate higher satisfaction with the MBCT-C program.

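### Hypothesis 5 counts pre-allocation recruitment as evidence that MBCT-C is acceptable, and extends the claim to parents although the satisfaction forms are described as measuring participants

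*Protocol article*

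**What the plan says.** Hypothesis 5, the last of the secondary hypotheses in the Introduction, reads: "The MBCT-C program will be acceptable to children and their parents as measured by recruitment, attendance, drop-out rates", and adds the MPSQ as a fourth marker.

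The order of enrolment and allocation is described twice:
- Recruitment and randomization procedures: "Once the desired sample size is enrolled, participants will be randomized to the MBCT-C or LST group", and then "The allocation will be made in a 1:1 ratio, ensuring equal representation of participants in each group".
- Procedure, by cohort: "As each cohort of 20 children is recruited, they will be randomly assigned to either intervention or control groups (10 per group".

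Study design uses a shorter list of acceptability markers, without recruitment: "A comparison of attendance and drop-out rates between the MBCT-C and LST groups will be one marker of program acceptability".

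On satisfaction, the Abstract says: "The Mindfulness Program Satisfaction Questionnaire (MPSQ) will assess participant satisfaction with the program". Procedure says: "The Client Satisfaction Questionnaire (CSQ-8) will measure participant satisfaction with both programs". The MPSQ section explains that "higher scores indicate higher satisfaction with the MBCT-C program", but does not say who fills in the form. The LSTSQ section describes an adapted eight-item form for participant satisfaction in the LST group.

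**The concern.** A marker of the acceptability of MBCT-C should reflect how families respond to MBCT-C. When they are recruited, they do not yet know which programme the child will receive. If hypothesis 5 is applied as written, good recruitment would be counted in favour of MBCT-C although it supports LST equally.

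The second part concerns whose view is measured. The hypothesis makes a statement about parents, while the forms described ask about participant satisfaction. A published conclusion that parents found the programme acceptable would rest on children's questionnaires and on behaviour that parent and child share, and a reader could not tell this from the hypothesis. Satisfaction stands beside efficacy in the aim given in the Abstract, so such a conclusion is likely to be reported.

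**Working it through.** No figure of the plan is in dispute, so the check sets the sections side by side.

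**1. Does recruitment precede allocation?** The two accounts differ on whether the whole sample or each cohort of 20 is enrolled first. In both, a family agrees to take part before the arm is known. The difference does not matter here.

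**2. What can a recruitment rate show?** Recruitment rate = families enrolled / families approached (or eligible).
- The planned numerator is 4 cohorts × 20 = 80. The denominator is not stated.
- Families who decline are never allocated, so the denominator cannot be divided by arm. There is one rate for the whole trial.
- That rate describes willingness to accept an even chance of MBCT-C or LST.
- The numbers per arm, 4 × 10 = 40 and 40, are fixed by the allocation scheme. They are allocation counts, not recruitment rates, and say nothing about acceptability either way.
- If enrolment is slow, Recruitment and randomization procedures provides for adding schools. Reaching 80 is therefore weak evidence of acceptability in itself; only the rate would inform.

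**3. Which of the four markers arise after allocation?**

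| Marker in hypothesis 5 | Timing | Specific to MBCT-C? |
|---|---|---|
| Recruitment | before allocation | no |
| Attendance | after allocation | yes |
| Drop-out | after allocation | yes |
| MPSQ | after the programme | yes |

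Three of four are usable as they stand. Study design already plans to compare attendance and drop-out between arms.

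**4. Where could a parent's view enter?**
- MPSQ, CSQ-8 and LSTSQ: described in terms of participant satisfaction. The randomised participants are children aged 8 to 12, and Ethical standards has children giving assent to participate while a parent or guardian signs consent.
- ERC: may be completed by a parent, but rates the child's emotion regulation, not the programme.
- Consent: a parental decision, but taken before allocation, so it shares the limitation in step 2.
- Attendance and drop-out: at this age, with sessions after school hours, they plausibly reflect parents' decisions in part, mixed with the child's.
- Interviews with children and parents about acceptability: mentioned in the Discussion as future research.

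The article thus describes indirect parent evidence and no satisfaction or acceptability form assigned to parents.

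**The case against.** The strongest defence is that hypothesis 5, unlike hypotheses 1 to 4, is not worded as a comparison with LST. It says that MBCT-C will be acceptable on several markers taken together, and nowhere does the plan say that recruitment alone would decide the matter. Where it does plan a between-arm comparison of acceptability, recruitment is left out. This stands, and it means that a lack of between-arm contrast is not in itself the fault. It does not rescue recruitment as a marker of MBCT-C: even without a comparison, the rate reflects entry to a two-programme trial.

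A reader might go further and infer that recruitment carries no information, citing 40 children in each arm. That does not follow. Those are allocation counts; the rate of enrolment among families approached is not fixed by 1:1 allocation and could be low. It is informative about the trial, only not specific to MBCT-C.

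A reader might also infer that the statement on parents rests on no data, or that no parent form exists. The article supports neither. Consent is a parent's act, and attendance and drop-out are partly so. The MPSQ section does not name its respondent, and a condensed article may leave a parent version to the full protocol. What can be said is that the wording shown points to participants, who are children.

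**Conclusion.** The point holds as a minor mismatch between a secondary hypothesis and its measures. Recruitment, one of four listed markers, is not specific to MBCT-C because it precedes allocation in both accounts of the procedure. For parents, one of two named groups, the evidence described is indirect and cannot be separated from the child's.

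Hypothesis 5 should not be called untestable: attendance, drop-out and child MPSQ scores remain valid markers of acceptability to children. The efficacy hypotheses 1 to 4 and their estimates are not touched.

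The conclusion rests on two assumptions: that families are not told the arm before they consent, as both accounts imply, and that participant means the child wherever satisfaction is mentioned. If the full protocol assigns the MPSQ to parents as well, the second part falls away and only recruitment remains.

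**What to change.** 1. Report recruitment, as enrolled over approached or eligible, under trial-level feasibility, and remove it from the markers in hypothesis 5.
2. Base the MBCT-C conclusion on post-allocation markers: uptake at session 1, attendance and drop-out, compared between arms with 95% intervals, plus child MPSQ scores. Session attendance is already to be recorded. The rule in Statistical strategy about missing more than three sessions serves the handling of missing data and should not be borrowed as an acceptability threshold.
3. Either limit hypothesis 5 to children, or keep the parent claim and have a parent complete the arm's existing eight-item form at T2 (MPSQ for MBCT-C, the adapted form for LST). The two forms have different content, so each is best read within its own arm.

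The cost is a change of wording and a narrower claim, or one short extra form per family. The intervals will be wide, which is a reason to show them. As an illustration, with the plan's 20% drop-out in both arms, 40 children per arm and no allowance for clustering within groups, the half-width for the difference is 1.96 × √(2 × 0.20 × 0.80 / 40) = 1.96 × 0.0894 = 0.175, or about 17.5 percentage points.

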## Method

### Study design

This is a quasi-experimental study that comparing an MBCT-C program to an active control groupthe. Demographic data will be collected at baseline. Assessment data will be collected at baseline (T1), post-intervention (T2), and 6-month follow-up (T3) (Figure 1). Participants will be randomly assigned to either MBCT-C or LST using a software-generated random sequence. A stratified block randomization method will ensure balanced distribution by gender and age. A comparison of attendance and drop-out rates between the MBCT-C and LST groups will be one marker of program acceptability. Participants' adherence to the intervention will be evaluated via session attendance, group activity participation, and homework assignment compliance. To reduce potential bias, assessors will be blind to group allocation.

